### Randomisation and blinding

Simple randomisation was used. The allocation sequence was generated using SPSS version 24.0. Each unique allocation code was placed in a sequentially numbered, opaque, sealed envelope (numbered 1–114) and stored by an independent custodian. After obtaining informed consent, the next envelope in sequence was opened, and the participant was assigned to either the control or treatment group (n = 57 per group). Because the two interventions could not be blinded to participants, only the outcome assessors, data managers, and statisticians were masked to group assignment. In the Case Report Form (CRF), group labels were replaced with the identifiers“A” and “B.” The master randomisation list (containing the sealed code linking A/B to actual groups) was generated by an external statistician using SAS software and is securely stored by the study administrator. It will remain concealed until after final database lock.

### Sample size

This is a parallel, two-arm, superiority RCT. A pilot study (Tong-bi Bushen formula for osteoporosis with kidney-deficiency/blood-stasis pattern) showed mean ± SD VAS improvements of 2.45 ± 0.53 (combination) vs. 2.07 ± 0.53 (Western medicine alone). Using an independent-samples t-test in PASS 15.0.1 (α = 0.05 two-sided, power = 0.95, 1:1 ratio) gave 51 participants per arm; allowing 10% attrition, 114 participants (57 per arm) will be enrolled. Data collection and registration All data will be captured in a paper/e-CRF. Investigators will be trained in patient communication, CRF completion and all rating scales. After consent, baseline demographics, BMD, TCM syndrome score, VAS, bone-turnover markers (β-CTX, PINP), inflammatory cytokines (TNF-α, IL-1), blood-stasis score and haematological indices (MCV, RDW-CV, MPV, PDW) will be collected. Follow-up visits occur every 4 weeks for 3 months. Original data and biological samples will be retained for a minimum of 5 years following the conclusion of the study.

An independent Data Monitoring Committee (DMC) consisting of external clinical epidemiologists, data managers and biostatisticians with no conflicts of interest will review safety, CRF accuracy and participant confidentiality every 6 months and will advise on protocol modification or early termination if warranted.

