**Anticipated Results:**

To our knowledge, this trial is the first clinical study of Rumo zhentong Yin for OPP, with the primary objective to provide robust clinical evidence supporting the integration of Traditional Chinese and Western medicine for OPP.

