### Inclusion criteria

Participants are eligible if they meet ALL of the following: Voluntary agreement to take part and signed informed consent.

Diagnosis of primary osteoporosis according to Western-medicine criteria. TCM syndrome differentiation of “blood-stasis syndrome”. ndividuals aged between 45 and 70 years, regardless of gender.Low-back or limb-joint pain for ≥3 months.

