### Exclusion criteria

Participants will be excluded if ANY of the following apply:

Fracture within the past 6 months.

Concomitant endocrine or metabolic diseases (hyperparathyroidism, Cushing’s syndrome, hyperthyroidism, gonadal hyper-function, diabetes), hematological diseases (myeloma, leukaemia), severe gastrointestinal diseases, or psychiatric/neurological disorders. Low-back pain attributable to lumbar-disc herniation, cervical spondylosis, or other clear causes.

Severe cardio-cerebrovascular disease, hepatic or renal insufficiency. Psychosis or inability to give informed consent. Participation in another clinical trial or completion of another drug trial within 3 months.

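### Limb-joint pain with another clear local cause is not excluded, and the 95% power rests on a difference and SD taken from a trial of a different formula

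*Protocol article*

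**What the plan says.** **Eligibility.** The Inclusion criteria section of the protocol article asks for primary osteoporosis, blood-stasis syndrome, age 45 to 70 and "Low-back or limb-joint pain for ≥3 months". The Exclusion criteria section removes "Low-back pain attributable to lumbar-disc herniation, cervical spondylosis, or other clear causes". It has no matching line for limb-joint pain. Recent fracture and a list of endocrine, metabolic, haematological, gastrointestinal, psychiatric and neurological conditions are excluded for everyone.

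**Sample size.** The Sample size section says "This is a parallel, two-arm, superiority RCT". Its inputs come from "A pilot study (Tong-bi Bushen formula for osteoporosis with kidney-deficiency/blood-stasis pattern"), which "showed mean ± SD VAS improvements of 2.45 ± 0.53 (combination) vs. 2.07 ± 0.53 (Western medicine alone"). From these, "α = 0.05 two-sided, power = 0.95, 1:1 ratio) gave 51 participants per arm", and "allowing 10% attrition, 114 participants (57 per arm) will be enrolled". The section gives no reason why values from that formula and pattern should carry over to Rumo zhentong Yin in blood-stasis syndrome, and shows no alternative SD. The abstract states that "this trial is the first clinical study of Rumo zhentong Yin for OPP".

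**The concern.** There are two separate weaknesses, and both bear on how the VAS result can be read.

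The first is the asymmetry in eligibility. A patient with osteoporosis, blood-stasis syndrome and a joint that hurts for a clear local reason meets every listed criterion. The same patient with back pain from a clear local reason does not. If such patients respond less to the formula, the between-group difference shrinks. Whatever their response, the trial no longer asks only about osteoporotic pain.

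The second is that the stated power depends on the ratio of 0.38 to 0.53, and both numbers come from one study of another product. If the spread of VAS change is larger here and the difference is not, power falls quickly. A non-significant result from a trial described as having 95% power would then be over-read as evidence of no effect.

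**Working it through.** **Inputs** (Sample size section): difference 2.45 − 2.07 = 0.38; SD 0.53 in each arm; two-sided α 0.05; power 0.95; 1:1 allocation; 10% attrition; independent-samples t-test.

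**1. Reproduce the plan.** By the normal approximation, n per arm = 2 × (1.960 + 1.645)² × 0.53² / 0.38² = 50.6, so 51. Attrition: 51 / 0.9 = 56.7, so 57 per arm and 114 in total. The noncentral t gives power 0.948 at 51 and reaches 0.95 at 52, a gap of no practical weight. The calculation is sound on its own inputs.

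**2. Vary the SD, holding the difference at 0.38.** Noncentrality = (0.38 / SD) × √(n / 2), with 2n − 2 degrees of freedom. At n = 51 and SD 1.0, for example, this is 0.38 × √25.5 = 1.92 on 100 degrees of freedom, giving power 0.48. The difference detectable with 95% power at 51 per arm is 0.721 × SD.

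| SD of VAS change | Power, 51 per arm | Power, 57 per arm | Detectable difference, 95% power, 51 per arm |
|---|---|---|---|
| 0.53 (plan) | 0.95 | 0.97 | 0.38 |
| 0.6 (assumed) | 0.89 | 0.92 | 0.43 |
| 0.7 (assumed) | 0.78 | 0.82 | 0.50 |
| 0.8 (assumed) | 0.66 | 0.71 | 0.58 |
| 1.0 (assumed) | 0.48 | 0.52 | 0.72 |

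At 51 per arm, power drops below 0.80 once the SD passes about 0.68, which is 0.68 / 0.53 = 1.28 times the planning value.

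**3. Illustrate dilution from pain of other origin.** Suppose a share q of enrolled patients gains nothing from the formula, and keep the SD at 0.53. The difference becomes 0.38 × (1 − q). With the same power formula at 51 per arm:
- q = 10%: difference 0.342, power 0.90
- q = 20%: difference 0.304, power 0.82
- q = 30%: difference 0.266, power 0.71

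The shares are assumptions. The article does not say how many such patients to expect.

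**4. Check whether the lack of a minimum VAS supports a large SD.** Take the plan's means and SD, and cap improvement at 2 points for an assumed share of patients who enter at VAS 2. At 51 per arm:
- 10% capped: power 0.92
- 20% capped: power 0.89
- 30% capped: power 0.86

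The SDs in the two arms stay at or below 0.53, so this cap narrows the spread. A cap at 1 point for 10% to 20% of patients does widen it, to between 0.60 and 0.75, with power 0.77 to 0.59. Neither case reaches an SD of 1.0.

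**The case against.** Borrowing planning values is ordinary when no trial of the formula exists. The source is a close relative: an add-on formula against Western medicine alone, in a pattern that includes blood stasis. That stands, and using the source is not itself a fault.

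A reader might infer more than the article supports, in three ways.
- **That true power is about 48%.** No SD of 1.0 appears anywhere in the article. Power also depends on the ratio of difference to SD, so a proportionately larger difference would preserve it. The analysed number may be nearer 57 than 51, since missing values are to be carried forward.
- **That this population is more heterogeneous than the source study's.** The source's entry criteria, baseline VAS and pain sites are not given, so the comparison cannot be made.
- **That the missing minimum VAS makes 0.53 untenable.** Step 4 shows that entry at VAS 2 costs little power and narrows the SD. More extreme entry values would cost more, but the article gives no baseline distribution. A threshold is also a trade-off against breadth of enrolment.

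It can also be said that the diagnostic requirements and general exclusions already remove much pain of other origin. They remove some. They do not cover limb-joint pain with a local cause, and the protocol thought the equivalent rule necessary for the back.

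**Conclusion.** The eligibility gap is real and can be read directly from the two criteria sections. Its size is unknown, because the share of patients affected is not stated. On the illustration in step 3, it would matter for power only if that share were substantial, but it blurs the target population at any share.

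The sample-size calculation is correct on its inputs, and 0.95 is not an error. What holds is that 0.95 has a narrow margin: an SD about 28% above the borrowed value takes power below 0.80 at 51 per arm if the difference stays at 0.38. Whether the SD here is larger cannot be judged from the article. This is an inexpensive improvement worth making while enrolment and follow-up continue. It does not show that the trial is underpowered.

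**What to change.** 1. **Eligibility.** For remaining enrolment, extend the existing other-cause exclusion to limb-joint pain through an ethics-approved amendment.
2. **Patients already enrolled.** Before unblinding, pre-specify a sensitivity analysis of the VAS outcome that leaves out those whose recorded medical history shows another clear cause of limb-joint pain. Table 1 schedules medical history at screening. Classify patients from those screening records, without knowledge of group, so that the exclusion does not depend on treatment.
3. **Power.** Compute the blinded pooled SD of VAS change from patients already followed; Table 1 has VAS at screening and days 30, 60 and 90. Report power and detectable difference at that SD beside the planning value of 0.53, without adding patients. Pooling without group labels inflates the SD only slightly: with a true difference of 0.38 and equal arms, √(0.53² + 0.19²) = 0.56. No unblinding or alpha adjustment is needed.

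**Cost.** The amendment comes late, since enrolment began on 12 September 2025 and closes on 31 December 2026, and final recruitment may slow slightly. The sensitivity analysis can be no better than what the medical history recorded; Table 1 lists no specific item for the cause of joint pain. The restated power may be less favourable than 0.95.

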### Statistical analysis

Statistical analyses will be performed with SPSS 24.0. Continuous variables will be presented as mean ±standard deviation (SD) if normally distributed, or as median (P25, P75) otherwise. Categorical variables will be summarised as frequencies and percentages (*n* [%]). Between-group comparisons of continuous endpoints be conducted using independent-samples t-test (normal) or Mann–Whitney U test (non-normal). Within-group changes over multiple visits will be analysed with repeated-measures ANOVA (normal) or generalised estimating equations (non-normal). If an interaction is significant, simple-effects analysis will follow. Unordered categorical variables will be compared with χ^2^ or Fisher’s exact test. Ordered categorical variables with the rank-sum test. All tests will be two-tailed, with a significance level set at P < 0.05. Missing values will be imputed by last-observation-carried-forward (LOCF) method.

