Visit window		−3∼0	Day 30 of treatment	Day 60 of treatment	Day 90 of treatment
Basic history taking					
Informed-consent signature		×	​	​	​
Demographics		×	​	​	​
General data form		×	​	​	​
Medical and prior-treatment history		×	​	​	​
Inclusion/exclusion check		×	​	​	​
Randomisation and enrolment		×	​	​	​
Screening variables					
Bone-mineral density (BMD)		×	​	​	​
Treatment administration					
Test group		​	×	×	×
Control group		​	×	×	×
Efficacy end-points (assessment visits)					
BMD measurement		×	​	​	×
TCM syndrome score		×	×	×	×
Pain score (VAS)		×	×	×	×
Bone-turnover markers (β-CTX, PINP)		×	×	×	×
Inflammatory cytokines (TNF-α, IL-1)		×	×	×	×
Blood-stasis syndrome score		×	×	×	×
Blood-cell indices		×	×	×	×
Safety observations					
Height		×	​	​	×
Blood pressure		×	​	​	×
Electrocardiogram		×	​	​	×
Haematology		×	​	​	×
Liver function		×	×	×	×
Renal function		×	×	×	×
Coagulation profile		×	​	​	×
Adverse-event log		​	×	×	×
Other items					
Concomitant medication / therapy		×			
Study closeout	Withdrawals and drop-outs	×			
	Compliance and safety evaluation form	×			
	Abnormalfindings record	×			
	Studycompletion status	×			
Review & sign-off		×			

Rumo zhentong Yin—composed of Ruxiang (frankincense), Moyao (myrrh), Xuejie (dragon’s blood), Jiangxiang (dalbergia wood), Sumu (sappan wood), Gansong (nardostachys), Xixin (asarum), and Tubiechong (ground beetle)—is an empirical formula created by national TCM master [name] for blood-stasis pain. Although preclinical studies support the anti-inflammatory, analgesic, and bone-protective effects of its ingredients, robust clinical evidence is still lacking (Shima et al., 2016; Lisowska et al., 2018).

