### Outcomes

Primary endpoints: Pain score: Visual Analogue Scale (VAS); Mechanism indicators: 1.Bone-mineral density (BMD); 2.Bone-turnover markers: β-CTX and PINP; 3.Inflammatory cytokines: TNF-α and IL-1.

Secondary endpoints:1.Blood-stasis syndrome score; 2.Hematological indices: serum MCV, RDW-CV, MPV and PDW.

Safety endpoints:Height, blood pressure, 12-lead ECG, routine hematology, liver and renal function tests, and coagulation profile.

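### The between-group VAS test makes no adjustment for baseline VAS, does not fix change or day-90 score, and lets a normality check decide what is estimated

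*Protocol article*

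**What the plan says.** Outcomes lists the primary measure without a form or time point: "Primary endpoints: Pain score: Visual Analogue Scale (VAS"). Statistical analysis gives a single between-group rule for all continuous endpoints: "Between-group comparisons of continuous endpoints be conducted using independent-samples t-test (normal) or Mann–Whitney U test (non-normal"). It names no covariate, normality test or threshold, and does not say which variable is checked for normality.

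A second sentence covers the repeated visits: "Within-group changes over multiple visits will be analysed with repeated-measures ANOVA (normal) or generalised estimating equations (non-normal"). It is followed by: "If an interaction is significant, simple-effects analysis will follow". The factors in that interaction are not defined.

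Baseline VAS is available for everyone. Table 1 marks "Pain score (VAS") at screening and at days 30, 60 and 90, and the data-collection text under Sample size confirms it: "After consent, baseline demographics, BMD, TCM syndrome score, VAS, bone-turnover markers (β-CTX, PINP"). The sample size rests on change, since the pilot study "showed mean ± SD VAS improvements of 2.45 ± 0.53 (combination) vs. 2.07 ± 0.53 (Western medicine alone"). On allocation, the article says "Simple randomisation was used", and it describes no stratification.

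**The concern.** Baseline pain is usually the strongest available predictor of later pain, and here it is collected but not used as a covariate. A between-group comparison that leaves it out is less precise than it could be at no extra cost. How much less depends on whether improvement or the day-90 score is compared. The sample size points to improvement, but the outcome and analysis sections do not say so.

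The normality condition adds a second uncertainty. A t-test compares means and yields the mean difference for which the trial is sized. A Mann-Whitney test addresses a shift in ranks and does not estimate that difference. Which of the two becomes the primary result is not known until the data are seen. With about 51 evaluable patients per arm, a comparison of means does not need this condition.

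**Working it through.** **Inputs from the article (Sample size).** Mean improvements 2.45 and 2.07, so the difference is 0.38; SD of improvement 0.53 in both arms; two-sided alpha 0.05; power 0.95; 51 per arm, 57 per arm after 10% attrition.

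**Reproducing the plan's figure.** n = 2 × [0.53 × (1.960 + 1.645) / 0.38]² = 50.56, so 51 per arm. 51 / 0.90 = 56.7, so 57 per arm. Both agree with the article. (The noncentral-t version gives 51.54, so 52, which is immaterial here.)

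**Assumptions, not in the article.** The correlation rho between baseline and day-90 VAS is not given, so a range is shown. Baseline and day-90 SDs are taken as equal, with common value s. Day 90, the last visit in Table 1, is taken as the time point.

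**Formulas.**
- Change score: 0.53² = 2s²(1 − rho), so s = 0.53 / √[2(1 − rho)].
- Raw day-90 score: SD = s.
- ANCOVA: residual SD = s√(1 − rho²).
- Variance ratio, ANCOVA to change score: (1 + rho)/2.
- Power = Φ(0.38 / [SD × √(2/51)] − 1.96).

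**Results at 51 per arm.**

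| rho | implied VAS SD | variance ratio, ANCOVA/change | power, change t-test | power, raw day-90 t-test | power, ANCOVA | n per arm for 95% power, ANCOVA |
|---|---|---|---|---|---|---|
| 0.3 | 0.45 | 0.65 | 95.2% | 99.0% | 99.4% | 33 |
| 0.5 | 0.53 | 0.75 | 95.2% | 95.2% | 98.7% | 38 |
| 0.7 | 0.68 | 0.85 | 95.2% | 80.1% | 97.5% | 43 |
| 0.8 | 0.84 | 0.90 | 95.2% | 62.9% | 96.8% | 46 |
| 0.9 | 1.19 | 0.95 | 95.2% | 36.7% | 96.0% | 49 |

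Starting from the SD instead: s = 1.0 gives rho = 1 − 0.2809/2 = 0.86 and a ratio of 0.93; s = 1.5 gives rho = 1 − 0.2809/4.5 = 0.94 and a ratio of 0.97.

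**Chance baseline imbalance, 57 per arm.** The 95% range is ±1.96 × s × √(2/57) = ±0.367s. An imbalance d moves a change-score estimate by −(1 − rho)d:
- rho 0.3, s 0.45: ±0.16 × 0.7 = ±0.12
- rho 0.7, s 0.68: ±0.25 × 0.3 = ±0.08
- s 1.0, rho 0.86: ±0.37 × 0.14 = ±0.05
- s 1.5, rho 0.94: ±0.55 × 0.06 = ±0.03

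**The two-stage choice of test.** This was simulated with 51 per arm and 20,000 null trials per setting, assuming a Shapiro-Wilk check in each arm, since the article names none. Type I error was 5.0% for normal data, 5.1% for skewed (gamma) data, 4.8% for VAS rounded to integers and 5.2% for VAS rounded to 0.1. The two tests disagreed on significance in 0.6% to 2.8% of null trials, and in 2.1% of 10,000 trials under the planned effect. About 10% of trials with exactly normal data were sent to Mann-Whitney, as were all trials with integer-rounded VAS.

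**The case against.** The strongest defence is that the plan is valid and consistent with its own sizing. The trial is sized with a t-test on improvement. If the same quantity is analysed, baseline enters by subtraction and power stays near 95%. The interaction sentence could also mean group by visit, with screening as one of the visits. Statisticians are masked until database lock, and a condensed article may leave covariates to a fuller document.

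Much of this stands. An unadjusted test is valid under randomisation, and on a change score the gain from ANCOVA is modest when rho is high. It does not settle the point. The article itself states the between-group test, so this is a choice made and not a detail deferred. The repeated-measures model is labelled within-group, is itself chosen by normality, and is not named as the primary contrast. Change is implied only by the sample-size paragraph.

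Two stronger readings are tempting. A reader might infer from simple randomisation that chance baseline imbalance passes straight into the estimate at about the size of the planned 0.38. The article does not support that: it points to improvement, where the consistent cases above give shifts of only ±0.03 to ±0.12. On a raw day-90 comparison the shift would be rho times the imbalance and could be large when rho is high, but the power loss in the table already counts it. A reader might also infer that the primary p-value is materially open to selection. The rule is stated in advance, the analysts are masked, and the simulated type I error is about nominal.

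**Conclusion.** The point holds as one of efficiency and definition, not of validity. Three things are wrong: baseline VAS is not used as a covariate, the choice between change and day-90 score is not fixed, and the estimand depends on a normality check.

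The size depends on which score is tested. Against a change-score t-test, ANCOVA reduces variance by 15% to 35% for rho 0.3 to 0.7 (VAS SD 0.45 to 0.68), but only by 3% to 7% if the VAS SD is 1.0 to 1.5 (rho 0.86 to 0.94). The larger gain and the larger SD cannot be claimed together, because the planned change SD of 0.53 ties them. Against a raw day-90 t-test the loss becomes serious once rho is well above 0.5. At rho 0.5 or below, the raw comparison keeps at least the planned power. ANCOVA does at least as well as either alternative at every rho shown.

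These figures rest on equal baseline and day-90 SDs and on an assumed rho. The simulated error rates rest on an assumed Shapiro-Wilk check.

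**What to change.** Before unblinding, specify one primary VAS analysis: a linear model of day-90 VAS on treatment and baseline VAS (ANCOVA, or the equivalent mixed model over visits). Report the adjusted mean difference with its 95% CI regardless of any normality test, and keep the Mann-Whitney test as a sensitivity analysis. The same adjustment can be applied to the other continuous endpoints that are measured at baseline, each with its own baseline value.

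The cost is a change of wording. The covariate is already collected, SPSS can fit the model, and the planned 51 evaluable per arm remains sufficient. Under Trial status, recruitment is registered to run to 31 December 2026, and the allocation code stays sealed until after database lock, so the change can be made as a dated amendment while the analysts are still masked.

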### Trial status

Participant recruitment was initially projected to start in January 2025 and close in June 2026, with follow-up assessments expected to finish in December 2026. However, due to preparatory delays, actual enrollment commenced on 12 September 2025, as registered with the International Traditional Medicine Clinical Trial Registry. Recruitment will continue until the registered closing date of 31 December 2026.

### Ethics and dissemination

The study will be conducted in accordance with the Declaration of Helsinki, the SPIRIT 2013 statement and the SPIRIT-TCM Extension 2018. Ethical a pproval has been obtained from the Medical Ethics Committee of Xi’an Hospital of Traditional Chinese Medicine, affiliated to Shaanxi University of Chinese Medicine (approval No. LLSCYJ2025085). The trial is registered with the International Traditional Medicine Clinical Trial Registry (ITMCTR2026000740). Any protocol amendments will be promptly submitted to the ethics committee for review and approval. Only individuals who provide written informed consent will be enrolled in the study. On completion, the findings will be submitted for publication in a peer-reviewed journal. Clinical insights and trial experience will be shared with participants and the wider public through conferences and publications. Authorship of the final report will be determined by individual contributions to the research.

